
#### Fidelity

All sessions of VRSCT will be audiotaped, and a selected number of sessions will be rated by an independent rater to ensure fidelity to the treatment protocol. Fidelity will be assessed by an independent rater with clinical expertise in autism, using a manual developed specifically for the STEPS intervention and based on key elements from the Cognitive Therapy Scale - Revised (CTS-R [49]). A total of 10 participant courses will be randomly selected across the recruitment period (3 from the early phase, 4 from the middle phase, and 3 from the late phase) to ensure representation across all trial phases and across therapists delivering the intervention. From each selected course, 3 sessions (one from the early, one from the middle, and one from the late phase of the course) will be randomly chosen for fidelity rating, resulting in 30 rated sessions in total. Time spent in VR will gradually increase during the first sessions and continue to build up across the intervention. The exact time spent in VR will be documented for each session.

#### Comparison Group

Participants in the comparison group will receive TAU alone, which typically comprises short-term psychoeducation provided by the clinical staff at the psychiatric facilities for autistic adults, following psychiatric assessment and diagnosis. Additionally, supportive counselling or practical assistance in daily life situations can be provided in community settings by social workers.

#### Criteria for Discontinuing or Modifying Allocated Interventions

Participants can choose to discontinue the interventions at any given time without any impact on their future psychiatric care. If participants experience a deterioration in their mental health condition during the intervention, this will be considered, and the intervention will be adjusted accordingly. Likewise, follow-up assessments and individual sessions in the intervention may be postponed if participants are unable to attend due to hospitalization. Any psychiatric hospitalization and its extent will be mapped upon trial completion.

#### Strategies to Improve Adherence to Intervention Protocols

Exposure to challenging social environments is a key component of the experimental intervention. Participants may encounter social situations that can provoke discomfort and anxiety. To prevent overwhelming the participant and reduce the risk of dropout, it is essential that the intervention be tailored to each participant’s optimal level of challenge. This ensures that difficult situations are addressed without exceeding their coping abilities. The therapists will maintain this balance through continuous dialogue with participants about their experiences and by promoting adherence to the intervention.

#### Relevant Concomitant Care and Interventions Permitted or Prohibited During the Trial

The prevalence of co-occurring psychiatric diagnoses is considered high among autistic adults, with ADHD (25.7%) being the most prevalent comorbid condition, followed by mood disorders (18.8%) and anxiety disorders (17.8%) [50]. The estimated prevalence of ADHD in the total autistic population is varying widely in the literature. Recent meta-analyses estimate the pooled point prevalence rate of ADHD in the autistic population to range from 28% to approximately 38% [51,52]. To enhance the ecological validity of the trial, co-occurring psychiatric conditions and associated medical treatments will not constitute exclusion criteria apart from medically untreated ADHD. As previously mentioned, participants with co-occurring ADHD must demonstrate a preliminary satisfactory treatment response to ADHD medication at the time of enrollment. This determination will be based on mutual agreement between the participant and the clinician responsible for their ADHD treatment, confirming that targeted ADHD symptoms are well managed. Additionally, no changes in the type or dosage of ADHD medication are permitted within the 4 weeks preceding enrollment in the trial. This criterion is essential due to the relatively high prevalence of co-occurring ADHD in individuals on the autism spectrum. Further, many adults are often being assessed for (and diagnosed with) ADHD while undergoing evaluation for autism. As a result, many potential participants may be titrating ADHD medication while being referred to the trial. To be able to effectively distinguish the effects of the trial intervention from those of ADHD medication, this criterion is essential. Furthermore, all psychopharmacological treatments will be thoroughly mapped and documented upon trial completion.

#### Provisions for Ancillary and Posttrial Care

All participants have access to the Danish public health care system before, during, and after participation in the trial. The experimental intervention is considered an add-on treatment to the standard treatment. If posttrial care is needed, it will be provided by the health care system and will follow national standards. If participants experience a significant deterioration in their mental health during the trial, the project may initiate a referral for outpatient psychiatric follow-up and treatment. Additionally, participants in the trial are covered by the Danish Patient Compensation Association, which evaluates and covers injuries resulting from health care treatment.

### Outcomes

Table 1 provides an overview of the outcome measures and their assessment time points.

**Table 1. T1:** Schedule of enrollment, intervention, and assessments

Content	Enrollment	Baseline assessment	Allocation	Intervention	Follow-up assessment 3 months post baseline	Follow-up assessment 6 months post baseline
Time points		t_0_			t_1_	t_2_
Information about the trial	✓					
Informed consent	✓					
Eligibility evaluation	✓					
SRS-2A^a^	✓					
Vocabulary and Matrix Reasoning (WAIS-IV^b^)	✓					
MINI^c^	✓					
Randomization			✓			
Interventions						
Comparison group (TAU^d^)				✓		
Experimental group (VRSCT^e^+TAU^d^)				✓		
Assessments						
Primary outcome						
SRS-2A^a^		✓ (administered at enrollment)			✓	✓
Secondary outcomes						
HiSoC^f^		✓			✓	✓
SRS-2AI^g^		✓			✓	✓
SIAS^h^		✓			✓	✓
ERT^i^ from CANTAB^j^		✓			✓	✓
EQ^k^		✓			✓	✓
Exploratory outcomes						
PSP^l^		✓			✓	✓
BRIEF-A^m^		✓			✓	✓
GSE^n^		✓			✓	✓
WHO-5^o^		✓			✓	✓
EQ-5D^p^		✓			✓	✓
SR-AS^q^		✓				
RBQ-3^r^		✓				
GAFS-8^s^		✓			✓	✓
CAT-Q^t^		✓			✓	✓
ASRS^u^		✓			✓	✓
BDI-II^v^		✓			✓	✓
TASIT-S^w^		✓			✓	✓
DACOBS^x^		✓			✓	✓
SSPA^y^		✓			✓	✓
Other measures						
CSQ^z^					✓	✓
NEQ^aa^					✓	✓
MPS-MSDV^ab^ (Only experimental group, 3 and 10 weeks post baseline)				✓		
SSQ^ac^ (Only experimental group, 3 and 10 weeks post baseline)				✓		
RTQ^ad^ (Only experimental group, 1 week post baseline)				✓		
I-VAS^ae^ (Only experimental group, 12 weeks post baseline)				✓		

a SRS-2A: Social Responsiveness Scale, Second Edition, Adult Form, Self-report.

b WAIS-IV: Wechsler Adult Intelligence Scale, Fourth Edition.

c MINI: Mini-International Neuropsychiatric Interview.

d TAU: treatment as usual.

e VRSCT: virtual reality-based social cognitive training.

f HiSoC: High-Risk Social Challenge task.

g SRS-2AI: Social Responsiveness Scale, Adult Form, Informant report.

h SIAS: Social Interaction Anxiety Scale.

i ERT: Emotion Recognition Task.

j CANTAB: Cambridge Neuropsychological Test Automated Battery.

k EQ: Empathy Quotient.

l PSP: Personal and Social Performance Scale.

m BRIEF-A: Behavior Rating Inventory of Executive Function - Adult Version, Self-Report.

n GSE: General Self-Efficacy Scale.

o WHO-5: WHO-5 Well-Being Index.

p EQ-5D: EuroQOL Five Dimensions Questionnaire.

q SR-AS: Sensory Reactivity in Autism Spectrum questionnaire .

r RBQ-3: Repetitive Behavior Questionnaire-3.

s GAFS-8: General Alexithymia Factor Score.

t CAT-Q: Camouflaging Autistic Traits Questionnaire.

u ASRS: Adult ADHD Self-Rating Scale.

v BDI-II: Beck Depression Inventory-II.

w TASIT-S: The Awareness of Social Inference Test short form.

x DACOBS: Davos Assessment of the Cognitive Biases Scale.

y SSPA: Social Skills Performance Assessment.

z CSQ: Client Satisfaction Questionnaire.

aa NEQ: Negative Effects Questionnaire.

ab MPS-MSDV: Multimodal Presence Scale, Modified Shortened Danish Version.

ac SSQ: Simulator Sickness Questionnaire.

ad RTQ: Readiness for Therapy Questionnaire.

ae I-VAS: Insight - Visual Analog Scale

#### Primary Outcome

The primary outcome is the change of social impairment from baseline to intervention cessation, measured at 3-month follow-up. At follow-up assessments, the observation period will comprise the last 2 weeks, instead of the previous 6 months, as at baseline assessment. The SRS-2A will be used to measure the level of social impairment [42]. The SRS-2A is a 65-item self-report rating scale designed to assess social impairments related to autism spectrum conditions [53]. SRS-2A consists of 65 items, scored on a 4-point Likert Scale (0‐3). Each item is scaled from 0 (never true) to 3 (almost always true), generating a total score ranging from 0 to 195. The SRS-2A provides a continuous measure of social impairment, where a higher score reflects a greater degree of difficulties with social interactions in everyday life. The SRS-2 has been extensively used in autism research across different age groups and has demonstrated strong validity and reliability in both children [54,55] and adults [56-58].

#### Secondary Outcomes

Secondary outcomes will assess changes in performance-based social skills, informant-reported social functioning, social anxiety, emotion recognition, and empathy:

Social skills performance will be measured using the High-Risk Social Challenge (HiSoC) task, a standardized performance-based task assessing social interpersonal skills [59]. HiSoC scoring comprises 3 primary factors, namely affect, odd behavior and language, and social interpersonal skills. Additionally, an overall impression of the performance is rated. These 3 factors and the general impression are added to calculate the HiSoC total score.Social impairment will be measured using the Social Responsiveness Scale, Adult Form, Informant report (SRS-2AI) [42]. The SRS-2AI, a 65-item rating scale, assesses the level of social impairment based on informant observation. Items are rated on a 4-point Likert Scale, from 0 (never true) to 3 (almost always true), generating a total score range of 0-195. The items, while similar in content to the self-report version, are adapted for the informant’s perspective. The SRS-2AI provides a continuous measure of social impairment, with higher scores indicating more severe difficulties with social functioning in everyday life.Social anxiety levels will be measured by the Social Interaction Anxiety Scale (SIAS) [60]. The SIAS consists of 20 items rated on a 5-point Likert scale, from 0 (not at all characteristic of me) to 4 (extremely characteristic of me). Items 5, 9, and 11 are positively worded items and require reverse scoring. The total SIAS, ranging from 0 to 80*,* is calculated by summing all item ratings, with higher scores indicating greater social anxiety experienced in social interaction*.*Emotion recognition ability will be assessed using the Emotion Recognition Task (ERT) from the Cambridge Neuropsychological Test Automated Battery (CANTAB) [61]. The ERT outcome measures include the percentage and count of correctly and incorrectly identified emotions displayed in images of facial expressions, as well as overall response latencies. These measures can be assessed across individual emotions or as an aggregate across all emotions.The level of empathy will be assessed using the Empathy Quotient (EQ), a 60-item questionnaire designed to measure empathy in adults with normal intelligence [62]. Each item is scored on a 4-point scale (strongly agree, slightly agree, slightly disagree, and strongly disagree), yielding a possible score from 0 to 80, with higher scores reflecting higher levels of empathy.

#### Exploratory Outcomes

##### Overview

Below, exploratory outcomes are grouped into the following categories: psychosocial functioning and quality of life, clinical symptoms, social cognition and performance, and other measures.

##### Psychosocial Functioning and Quality of Life

This will be measured using the following outcomes: (1) the Personal and Social Performance scale (PSP) [63] to assess daily life social functioning; (2) the Behavior Rating Inventory of Executive Function - Adult Version, Self-Report (BRIEF-A) [64,65] to assess everyday executive function; (3) the General Self-Efficacy Scale (GSE) [66] to assess perceived self-efficacy; (4) WHO-5 Well-Being Index (WHO-5) [67] to assess subjective, psychological well-being; and (5) the EuroQOL 5D questionnaire (EQ-5D) [68,69] to assess health-related quality of life and to conduct cost-effectiveness analysis.

##### Clinical Symptoms

This will be measured using the following outcomes: (1) Sensory Reactivity in Autism Spectrum (SR-AS) questionnaire [64] to assess sensory reactivity; (2) the Repetitive Behavior Questionnaire-3 (RBQ-3) [70] to assess restricted and repetitive behaviors and interests; (3) the General Alexithymia Factor Score (GAFS-8) [71] to assess alexithymia; (4) the Camouflaging Autistic Traits Questionnaire (CAT-Q) [72] to assess social camouflaging behaviors; (5) the Adult ADHD Self-Report Scale (ASRS) [73] to assess ADHD symptoms; and (6) the Beck Depression Inventory-II (BDI-II) [74] to assess depressive symptoms.

##### Social Cognition and Performance

This will be measured by the following outcomes: (1) the Awareness of Social Inference Test short form (TASIT-S), part 2 Social Inference, Minimal) [75,76] to assess ToM and complex emotion comprehension; (2) the Davos Assessment of the Cognitive Biases Scale (DACOBS) [77] to assess cognitive biases; and (3) the Social Skills Performance Assessment (SSPA) [78] to assess social communication skills (competence and appropriateness of conversational skills).

##### Other Measures

These measures related to participants’ experiences of the intervention will be assessed using the following measures: (1) the Client Satisfaction Questionnaire (CSQ) [79] to assess satisfaction with the assigned intervention; the Negative Effects Questionnaire (NEQ) [80] to assess negative events and outcomes; (2) the Multimodal Presence Scale, Modified Shortened Danish Version (MPS-MSDV) [81] to assess involvement and immersion into the VR environments (only administered to participants in the experimental group); (3) the Simulator Sickness Questionnaire (SSQ) [82] to assess simulator sickness related to being in VR (only administered to participants in the experimental group); (4) the Readiness for Therapy Questionnaire (RTQ) [83] to assess attitudes and readiness for therapy aimed at resolving problems; and (5) an Insight-Visual Analog Scale (I-VAS) to assess level of insight into challenges related to social interaction. Participants and therapists will indicate, on a scale from 1 to 10, the extent to which the intervention has increased the participant’s awareness of their challenges with social interaction, with 1 representing no increased awareness and 10 indicating the highest possible increase in awareness. I-VAS will be administered by the therapists in the intervention and only to participants in the experimental group upon completion of the intervention.

### Sample Size and Power Calculation

The sample size calculation is based on detecting a between-group difference in the primary outcome, the SRS-2A, at cessation of the intervention (3 months post baseline). Previous studies have reported considerable variation in the SD of the social responsiveness scale total score when assessing social impairment in autistic adults [25,56,58]. As a result, we have not been able to determine the minimal clinically important difference. Therefore, we have based our sample size calculation on a medium effect size (Cohen *d*=0.5), which corresponds to a difference of 0.5 SD between the experimental group (VRSCT+TAU) and the comparison group (TAU). With 80% power and a 2-sided significance level of α=.05, 63 participants are required in each group to detect this difference. To account for an anticipated 10% dropout rate, we plan to recruit a total of 140 participants. Sample size calculation is based on a medium effect size (Cohen *d*=0.5) in accordance with established practice in clinical trial design. However, it may not reflect the smallest change considered clinically meaningful. Clinical significance will therefore be interpreted alongside observed effect sizes and CIs in subsequent reporting to ensure meaningful interpretation of trial outcomes.

### Recruitment

The project group has established strong collaborations with several public and private outpatient facilities in Denmark, which are specializing in the clinical assessment and diagnosis of autism in adulthood. Based on the collaboration agreement, the multidisciplinary staff at these sites will routinely approach relevant participants and refer them to the VIRTU Research Group. To foster collaboration and ensure ongoing referrals to the trial, staff from the VIRTU Research Group will regularly attend conferences and meetings at the various recruitment sites and invite clinicians to discuss potential participants.

### Allocation

#### Sequence Generation

Participants who provide signed informed consent and meet the eligibility criteria will be randomly allocated to receive either TAU or VRSCT+TAU upon completion of the baseline assessment. Randomization will be performed using a centralized, automated, computer-generated randomization module in the online REDCAP (Research Electronic Data Capture; Vanderbilt University) system (refer to “Data Management” section). A stratified block randomization with a concealed randomization sequence will be used, with block sizes that are variable and unknown to the investigators. Randomization will be stratified by site and sex. The allocation of the randomized intervention will remain concealed to investigators and assessors until the statistical analyses of outcome data have been completed.

#### Concealment Mechanism

When a participant has completed the baseline assessment, the trial assessor, who is responsible for conducting the assessment, will email one of the trial therapists responsible for generating the allocation sequence. The assessor will then receive a confirmation email acknowledging receipt only. The trial therapist has exclusive access to the randomization module in REDCAP (refer to “Data Management” section), ensuring that assessors are blinded to intervention allocation.

#### Implementation

Allocation sequences are generated by one of the trial therapists. Enrollment and assignment to the interventions are carried out by the therapists who are conducting the interventions in the experimental group.

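### The article gives sequence generation, sole module access, enrolment and assignment to the unblinded therapists, so its claim of a concealed allocation sequence is unsupported

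*Protocol article*

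**What the plan says.** Three adjacent subsections of the protocol article, under Allocation, describe the process.

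- **Sequence Generation.** Allocation follows consent, confirmation of eligibility and the baseline assessment, and uses a central computerised REDCap module. Randomisation is stratified by site and sex, in blocks "with block sizes that are variable and unknown to the investigators". It also says: "The allocation of the randomized intervention will remain concealed to investigators and assessors until the statistical analyses of outcome data have been completed".
- **Concealment Mechanism.** After baseline, the assessor "will email one of the trial therapists responsible for generating the allocation sequence" and gets back only an acknowledgement. "The trial therapist has exclusive access to the randomization module in REDCAP", the stated result being "ensuring that assessors are blinded to intervention allocation".
- **Implementation.** This subsection sets out the roles: "Allocation sequences are generated by one of the trial therapists. Enrollment and assignment to the interventions are carried out by the therapists who are conducting" VRSCT.

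Other sections bear on this. Blinding says that therapists are not blinded. Trial Oversight and Management places the principal therapist on the Project Management Group. Consent says that psychologists of the research group obtain consent, without saying whether these are the therapists. Data Management mentions a data manager and a REDCap audit trail.

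**The concern.** Allocation concealment means that whoever decides whether and when a person enters the trial cannot know the next assignment. It is normally secured by separating the person who makes and holds the list from those who enrol and treat. Here one unblinded role is given all of these tasks. Two subsections say that a therapist generates the sequence, so a single slip of wording is less likely.

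Assessor blinding does not fill the gap. It protects measurement after allocation, not selection before it. The primary outcome is also a self-report by participants who know their arm, so it gains little from assessor blinding.

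If an enrolling therapist could foresee the arm, the entry of people expected to do well could be timed or steered. Covariate adjustment would correct only for what is measured. Motivation and expected response are not among the covariates. The Limitations section does not mention the issue.

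**Working it through.** The article states no figure on this point, so the check is first a comparison of texts and then an illustration of size.

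**Step 1: the property claimed against the procedure described**

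| Property | Sequence Generation | Concealment Mechanism, Implementation, Blinding |
|---|---|---|
| Who makes the sequence | The central REDCap module | One of the trial therapists (stated twice) |
| Who can open the module | Not stated | The trial therapist only |
| Who enrols and assigns | Not stated | Therapists delivering VRSCT |
| Block sizes | Unknown to investigators | Therapist generates the sequence; no statement that therapists cannot see block sizes |
| Allocation hidden until analysis | From investigators and assessors | Therapists unblinded; principal therapist on the management group |

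Nowhere does the article say that someone independent of enrolment and treatment makes or holds the list, or that therapists cannot see upcoming assignments.

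**Step 2: how predictable assignments could be**

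Allocation is 1:1, and under full concealment a guess is right 50% of the time.

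(a) *The list is visible to its maker.* Every next assignment can be known: 100%.

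(b) *Only past allocations in a stratum are known, and the guess is always the arm that is behind.* This rule does not require knowing the block sizes. For a completed block of size n, the expected number of correct guesses is n/2 + 2^(n−1)/C(n, n/2) − 1/2.

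- n = 2: 1 + 2/2 − 0.5 = 1.5
- n = 4: 2 + 8/6 − 0.5 = 2.833 (2.833/4 = 70.8%)
- n = 6: 3 + 32/20 − 0.5 = 4.1
- n = 8: 4 + 128/70 − 0.5 = 5.329

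The article says that block sizes vary but does not give them. Taking mixes with sizes equally likely as an assumption:

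| Assumed mix | Complete blocks | Simulated, 35 per stratum |
|---|---|---|
| 2/4 | (1.5 + 2.833)/6 = 72.2% | 71.5% |
| 4/6 | (2.833 + 4.1)/10 = 69.3% | 68.6% |
| 4/6/8 | (2.833 + 4.1 + 5.329)/18 = 68.1% | 67.4% |

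The simulation assumes four strata (140/4 = 35). It is slightly lower because the last block in a stratum is usually cut off. The range is about 67% to 72%. Varying the block size therefore lowers predictability only modestly for someone who sees past allocations.

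**Step 3: how much of the trial a change could still reach**

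The Results section reports 97 enrolled by December 2025: 140 − 97 = 43, and 43/140 = 31%. It expects enrolment to finish in April 2026.

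**The case against.** The strongest defence is that a therapist generating the sequence may mean no more than running the automated module. The therapist acts after an email about one participant who has completed baseline, which fits case-by-case use at least as well as a list written in advance. A module set up by someone else could keep upcoming assignments and block sizes hidden. This stands. A reader might infer that allocation was not concealed, or that assignments were foreseen; the article does not establish either. Even on this reading, however, two subsections are worded wrongly and enrolment still sits with the people who assign and treat.

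Second, the room to steer entry is limited. Referrals come largely from outside clinics, social services, a recruitment platform or the participants themselves. Several entry criteria are measured or documented. Psychologists take consent, and an assessor without module access completes baseline before randomisation. This narrows the opportunity but does not close it: the article does not say that the consenting psychologists are separate from the therapists, and Implementation names the therapists for enrolment.

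Third, the primary analysis adjusts for baseline SRS-2A, the stratification variables, social anxiety, alexithymia and social function. That deals with measured imbalance, so it would be too strong to say that nothing later helps. It does not deal with unmeasured selection.

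Fourth, the promise to keep allocation from investigators is false only if therapists count as investigators, a term the article does not define. The wording is unclear rather than demonstrably untrue.

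A condensed article may leave detail to the full protocol, but these roles are stated in it, not left out.

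**Conclusion.** The concern holds as a contradiction and an unsupported claim. As written, the unblinded therapists generate the sequence, alone control the module, enrol, assign and treat, while the preceding subsection claims a concealed sequence with hidden block sizes. A reader cannot accept the concealment claim on this text, and the validity of the randomised comparison depends on it.

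What is not shown is that concealment failed in practice. The size is conditional: up to 100% foreseeable if the list was visible, and about 67% to 72% if only past allocations were tracked. The latter rests on assumed block mixes and four assumed strata. The finding does not depend on these figures.

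**What to change.** **For any remaining allocations**

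- A person independent of enrolment and treatment creates and holds the stratified list and its block sizes. This could be the data manager, or someone in the independent statistician's unit other than the blinded analyst. That independence must be confirmed first: the article says nothing about the data manager's contact with participants, and states absence of contact only for the statistician.
- Therapists' REDCap rights are limited to receiving one assignment, after consent, eligibility and baseline have been recorded.
- Enrolment and consent stay with staff who hold no randomisation rights.

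**For participants already randomised**

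- Use the REDCap audit trail to document who created the list and who could view it.
- Report baseline SRS-2A against the predictability of each assignment within stratum. This check would be weak in small strata, so a null result would not by itself prove concealment.

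**In the text**

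- Reconcile Sequence Generation, Concealment Mechanism and Implementation: say who made the list, what therapists can see, and what enrolment by therapists means.
- Define investigators, and reconcile the statement that allocation stays hidden from them with the Blinding and Trial Oversight sections.

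**Cost.** A change of user rights and a short amendment. If a new list is uploaded, some open blocks are abandoned, with a small loss of balance within strata. The prospective benefit depends on how many allocations remain and may be small if enrolment has closed. The audit-trail report and the corrected text are worthwhile in either case.
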